## 5.5 Clinical endpoints

### 5.5.1 Response assessment

Response will be assessed clinically and radiological (CT scan or MRI). The RECIST (version 1.1) criteria for response will be used, encompassing the categories complete response, partial response, stable disease progressive disease and inevaluable for response (Eisenhauer 2009).

In addition, individual tumor measurements will be collected in order to calculate % change in axis length (long axis for metastatic lesions; short axis for lymph nodes). All tumor assessments are conducted by the investigator, and all responses are independently reviewed by a radiologist.

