| pharmacokinetics                |          | 0-2h, day 2,3,4 and 7
1h and day 4 or 7     |                                                                         |              |

**Chemistry panel:** Na, K, Ca, Mg, Alb, creatinin, bilirubin,  $\gamma$ GT, AF, ASAT, ALAT, LDH.

**Hematology:** Hb, Ht, WBC, ANC, Platelets

**Radiology:** MRI or CT images will be required within 4 weeks before start, every 2 months during the first year of treatment and thereafter every 3 months until progressive disease. CT scans or MRI scans will be performed according to standard procedures. The radiologist will review any responses using RECIST 1.1 independently from the investigator.

**18FDG-PET:** scans will be required within 4 weeks before start and 4 weeks after start.

**Immuno-PET-CT scan:** The first five patients will be asked to undergo in total 5 immuno-PET scans and 5 simultaneous venous blood samples at 0-2h, day 2,3,4 and 7 after administration of Zr -cetuximab in order to study pharmacokinetics of Zr -cetuximab in more detail. The following patients will undergo in only 2 immuno-PET scans, at 0-2h and 4 or 7 days after Zr –cetuximab administration.

Follow up will last till progressive disease and/or death of the patient. In the case of progressive disease, the choice of any following line palliative chemotherapy is at the discretion of the investigator.

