### 7.2 Statistical design and analysis

#### 7.2.1 Part one

Primary endpoint: maximum 11 patients + 1 allowing for drop-outs = 12

Statistical design: probability

We will analyze  $^{89}\text{Zr}$ -cetuximab uptake in non-hepatic tumor lesions as binary variable (present/absent). We assume that all patients with response (i.e. complete response and partial response) according to RECIST 1.1 criteria and half the patients with stable disease according to RECIST 1.1 criteria will show uptake. According to previous publications we estimate that  $\geq 10\%$  of patients will show response and 30% have stable disease. Thus assuming that the proportion of patients with uptake is 0.25 or more, the probability of seeing no uptake in a cohort of 11 patients is less than 0.05. This has been calculated using a binomial distribution ( $n=11$ ,  $p=0.25$ ).

Stopping rule: The trial will stop if 11 patients do not show uptake. The trial will proceed to part two when the first patient with uptake is seen.

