#### 7.2.2 Part two

Primary endpoint: 35 patients (including all patients of part one) + 3 allowing for drop-outs = 38

Statistical design: Comparison of two independent groups of binary data

We are planning a study of independent cases (= all patients with complete response, partial response and stable disease according to RECIST 1.1 criteria) and controls (= patients with progressive disease according to RECIST 1.1 criteria) with 1.5 control(s) per case. We assume a false positive rate of 0.2 in the true negative's (= patients with progressive disease according to RECIST 1.1 criteria) because other downstream targets of the EGFR/RAS pathway may be mutated, thus interfering with response to cetuximab treatment. Measurement of cetuximab uptake using  $^{89}\text{Zr}$ -cetuximab will only be clinically relevant if we identify  $\geq 70\%$  of patients correctly as failures to treatment. Type I error probability has been set at 0.1, the power at 0.9. We will use a continuity-corrected chi-squared statistic or Fisher's exact test to evaluate this null hypothesis.

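### The SD/PD call that forms the part-two groups is not blinded to 89Zr uptake, and the protocol does not say how far the radiologist's review reaches or whose reading is analysed

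*Protocol*

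**What the plan says.** Section 7.2.2 forms two groups for the primary part-two test. Cases are "all patients with complete response, partial response and stable disease according to RECIST 1.1 criteria"; controls are "patients with progressive disease according to RECIST 1.1 criteria". CR, PR and SD fall on the same side, so the boundary that matters is SD against PD.

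Two places say who reads the scans.

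- Section 5.5.1: "All tumor assessments are conducted by the investigator, and all responses are independently reviewed by a radiologist". The same section makes the call partly clinical: "Response will be assessed clinically and radiological (CT scan or MRI".
- Table 1, footnote 3: "The radiologist will review any responses using RECIST 1.1 independently from the investigator".

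On timing, Section 5.5.2 puts the immuno-PET scans on day 1 and on day 4 or 7, with extra days in five patients. Table 1 puts follow-up tumour measurements at every 2 months in the first year. Section 7.2.1 moves the trial to part two once the first patient with uptake is seen, so uptake is read while patients accrue. Those part-one patients are also counted in part two.

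The protocol does not say that the investigator or the radiologist is kept from the 89Zr result. It does not say which category is used if the two readers disagree.

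**The concern.** The trial asks whether tumour uptake predicts benefit. That needs an outcome called without knowledge of uptake. Here the outcome is called by the investigator, in a single-group study with no blinding described, about two months after the predictor has been imaged. Sections 1 and 2.3 also state the expected direction: patients who do not respond are thought to have too little drug in the tumour. If uptake influences a borderline SD/PD call, the influence will tend to run towards the association being tested.

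An independent radiological review would be the natural safeguard, but it falls short in two ways. Its scope is unclear at the SD/PD boundary, and being independent of the investigator does not mean being unaware of the PET scan.

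**Working it through.** **1. What 'response' covers.** Section 7.2.1 uses the narrow sense: "We assume that all patients with response (i.e. complete response and partial response". Section 5.5.1 uses the broad sense for the RECIST criteria: "encompassing the categories complete response, partial response, stable disease progressive disease and inevaluable for response". Section 7.1 likewise lists RECIST response as a set of categories. In the narrow sense the radiologist would not see most SD and PD calls; in the broad sense the review covers every patient. The text does not settle which is meant. In both senses, blinding to PET and the choice of reading remain open.

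**2. The plan's own sample size.** Section 7.2.2 gives 35 patients and 1.5 controls per case, so 35/2.5 = 14 cases and 21 controls. Reading its 0.7 and 0.2 as the two uptake rates, the exact power of a two-sided Fisher test at 0.10 is 0.907. The stated 0.9 is reproduced, and the sample size is not in question.

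**3. Sensitivity to a leak.** Inputs:

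- N = 35 and type I error 0.10, with Fisher's exact or the continuity-corrected chi-squared test (7.2.2). Sidedness is not stated; two-sided is assumed.
- CR/PR 10% and SD 30% (7.2.1), leaving PD 60%.
- Uptake u = 0.25 (the lower bound in 7.2.1), or u = 0.7 × 0.4 + 0.2 × 0.6 = 0.40 (from the 7.2.2 rates).
- f, the share of SD/PD calls that follow the PET result. **This is an assumption; the documents give no figure.** CR and PR labels are left alone.

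Uptake and true category are taken as independent, so there is no real association. A leak turns uptake-positive PD into SD and uptake-negative SD into PD, each with probability f:

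- benefit, uptake: u(0.4 + 0.6f)
- benefit, no uptake: (1 − u)(0.4 − 0.3f)
- PD, uptake: 0.6u(1 − f)
- PD, no uptake: (1 − u)(0.6 + 0.3f)

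The false-positive rate is the multinomial probability, summed over all 2×2 tables with 35 patients, of those with p ≤ 0.10. The expected number of changed calls is 35 × f × [0.6u + 0.3(1 − u)].

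| u | f | Changed calls | Fisher | Corrected chi-squared |
|---|---|---|---|---|
| 0.25 | 0 | 0 | 0.061 | 0.041 |
| 0.25 | 10% | 1.3 | 0.096 | 0.069 |
| 0.25 | 20% | 2.6 | 0.187 | 0.145 |
| 0.40 | 0 | 0 | 0.075 | 0.047 |
| 0.40 | 10% | 1.5 | 0.121 | 0.078 |
| 0.40 | 20% | 2.9 | 0.244 | 0.173 |

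**4. Spurious difference at f = 20%.**

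- u = 0.25: uptake in the benefit group is 0.25 × 0.52 / (0.25 × 0.52 + 0.75 × 0.34) = 0.130/0.385 = 0.338. In the PD group it is 0.120/0.615 = 0.195. The difference is 0.14.
- u = 0.40: 0.208/0.412 = 0.505 against 0.192/0.588 = 0.327. The difference is 0.18.

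**The case against.** The best defence has four parts.

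- **The review may already cover everyone.** The sentence in 5.5.1 closes a section on response assessment that lists SD and PD among the categories. A reader might infer that the radiologist sees only CR and PR, which at 10% would be 3 or 4 of 35 patients. The documents do not establish that; the wording is ambiguous. This part stands, but a review of every patient would still not be blinded to PET.
- **Nobody is said to hold the PET result.** A reader might infer that the investigator has it from week 1. The protocol does not say so. Section 5.5.3 has values recorded in a spreadsheet, and the part-one rule requires only that someone knows when the first positive patient appears. What stands is that the investigator can know, not that the investigator does.
- **RECIST 1.1 limits discretion.** It is based on measurement, and individual lesion measurements are collected. This makes a large leak less likely. It does not remove judgement, since 5.5.1 also allows clinical assessment.
- **The inflation is conditional.** At a 10% leak the rate stays below 0.10 in three of the four settings, partly because both tests are conservative at this size. This is correct.

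Reading detail can also be left to an imaging charter or a SAP. But this protocol does set out who reads and who reviews, and an analysis plan cannot restore blinding once scans have been read with uptake known.

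**Conclusion.** The concern holds in a limited form. The primary groups turn on the SD/PD call. The investigator conducts the assessments after the immuno-PET has been acquired. No rule blinds either reader to uptake or names the reading that counts, and the scope of the radiologist's review is ambiguous. Knowledge of uptake could therefore bias the tested association.

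The size rests on an assumed leak rate. At 10% of SD/PD calls the false-positive rate is about 0.07 to 0.12 against a nominal 0.10, which is little or no excess. At 20%, fewer than three changed calls on average in 35 patients, it is 0.145 to 0.244 and exceeds 0.10 in every setting examined. The ranges run over uptake of 0.25 and 0.40 and both named tests. A reader might go further and infer that bias will occur or that an observed association would be an artefact. The documents do not support that: they leave the route open and say nothing about how often it would be used.

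**What to change.** In Section 5.5.1 and Table 1 footnote 3, state that the radiologist already named assigns the RECIST 1.1 category (CR, PR, SD or PD) for every patient, without access to the 89Zr-cetuximab images or uptake values. In Section 7.2.2, state that this reading defines cases and controls. The wording also removes the ambiguity over 'responses'.

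The cost is a protocol wording change and somewhat more scans for the same radiologist to read. No extra reader, scan or patient is needed; the sample size stays at 35, or 38 with drop-outs. Two additions are optional: a sensitivity analysis on the investigator's reading, and locking the uptake values before the first follow-up CT or MRI.

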### 5.5.2 Immuno-PET acquisition

All PET studies will be performed on a Gemini TF-64 PET-CT scanner. In 5 patients, whole-body PET scans (trochanter major femora-skull vertex) will be acquired after a single injection of 37 MBq  $^{89}\text{Zr}$ - cetuximab on day 1 (0-2h after injection), day 2, 3, 4 and 7 for pharmacokinetic purposes. In the remaining patients, PET scans will be acquired on day 1 and day 4 or 7 depending on the optimal time point determined with the results of the first five patients. The venous infusion line inserted for administration of unlabelled cetuximab will be used for  $^{89}\text{Zr}$ - cetuximab injection as well. At each scan a second venous cannula will be inserted for blood sampling. Blood samples will be used to measure absolute radioactivity concentration in whole blood and plasma. Prior to each whole-body PET scan, a 30 mAs low-dose CT scan will be acquired for attenuation correction and localization purposes. PET scans will consist of 10-12 bed positions, depending on the length of the patient, of 5 min each. Total acquisition time per scan, including LD-CT, will be below 90 min.

### 5.5.3 Data-analysis $^{89}\text{Zr}$ - cetuximab scans

All PET data will be corrected for dead time, scatter, randoms, decay, tissue attenuation. PET/CT data will be reconstructed with TF-OSEM, resulting in a transaxial spatial resolution of ~7 mm in the centre of the field of view. Regions of interest (ROIs) will be defined using the CT images which are co-registered to the PET/CT data. ROIs around the organs which accumulate  $^{89}\text{Zr}$  (e.g. liver, lung, and metastatic lesions) will be drawn manually directly on the PET images. All tissue concentrations will be related to the blood concentration. The radioactivity concentrations in all regions for all imaging time points should be recorded digitally in a spread sheet. A tumor lesion will be scored positive if there will be uptake above background, being defined as  $\text{SD}(\text{background}) + 1$ .

For pharmacokinetics, absorbed dose calculations will be made using the Olinda/EXM 1.0 software package, based on the Medical Internal Radiation Dose scheme (Stabin 2005).

### 5.5.4 [18F]-FDG-PET

To allow for flexible logistics, these studies will be conducted using either PET-CT or PET, using the same scanner for each individual. Studies and scanner calibrations will fully comply with the EANM guidelines (EJNM 2010, Boellaard 2010). The dose of [18F]-FDG will be about 185 MBq for PET-CT. Scan trajectory (WB-mode) will be adapted according to metastatic pattern in individual patients, and will remain the same after the baseline scan. Data-analysis will be done using in-house developed software, yielding SUV max, 70%VOI, 50%VOI, normalized for serum glucose, body weight, LBM and BSA.

### 5.5.5 Assessment skin toxicity

Cutaneous adverse effects due to EGFR inhibition are most commonly a papulopustular reaction involving most frequently areas of the head and upper trunk. Changes of the hair and nails may also occur. The CTC 4.0 criteria appear to be insufficiently specific to monitor these changes, as they rely heavily on body surface area as a determinant for rash severity. Thus, they fail to account for the location, i.e. upper trunk and face, and the subjective discomfort of EGFR inhibitor mediated rash. An EGFR inhibitor specific grading system has been developed which reflects the specific nature of an EGFR inhibitor-mediated skin toxicity (Melosky 2009, see table 3 below).

**Table 3** Grading system for skin rash mediated by EGFR inhibition

| Grade    | Skin phenotype                                                              | Symptoms                   | Effect on daily life                    | Rating   |
|----------|-----------------------------------------------------------------------------|----------------------------|-----------------------------------------|----------|
| Grade 1  | macular or papular eruptions or erythema                                    | no associated symptoms     |                                         | mild     |
| Grade 2A |                                                                             | pruritus or other symptoms | symptomatic but tolerable               | moderate |
| Grade 2B |                                                                             |                            | symptomatic interfering with daily life |          |
| Grade 3  | severe, generalized erythroderma or macular, papular or vesicular eruptions |                            |                                         | severe   |
| Grade 4  | generalized exfoliative, ulcerative or blistering skin toxicity             |                            |                                         |          |

## 6 Investigational Medicinal Product

### 6.1 Production, procedures and analysis of $^{89}\text{Zr}$ -cetuximab

Using standard procedures for the production of  $^{89}\text{Zr}$ -mAb conjugates, several clinical  $^{89}\text{Zr}$ -immuno-PET studies have been performed, are ongoing, or will be started shortly. In these ongoing studies safety was confirmed.  $^{89}\text{Zr}$  is coupled to cetuximab via the bifunctional chelate desferal.  $^{89}\text{Zr}$  will be produced at the VUmc campus by Cyclotron BV according to procedures essentially as described before (Verel 2003). Radiochemical purity of the purified  $^{89}\text{Zr}$  used for labeling will be according to the specification as described in same paper.  $^{89}\text{Zr}$ -MAB conjugates produced in this way were found to be fully stable in vitro, in tumor-bearing nude mice (Perk 2005, Aerts 2009), as well as in patients ([name] pers. comm.). Using the same procedures, the following conjugates have been produced and administered to patients without any adverse event:  $^{89}\text{Zr}$ -cMAB U36 (Borjesson 2006),  $^{89}\text{Zr}$ -ibritumomab tiuxetan (zevalinTM) (Perk 2006),  $^{89}\text{Zr}$ -rituximab (ritixanTM), and  $^{89}\text{Zr}$ -trastuzumab (herceptinTM).

Radiolabeling of cetuximab with  $^{89}\text{Zr}$  will be performed by the department of Otolaryngology/Head & Neck Surgery of the VU University Medical Centre according to Standard Operating Procedures (SOPs) within the premises of the Radionuclide Centre (RNC) of the Department of Nuclear Medicine & PET research. The whole process will be performed according to state-of-the-art Good Manufacturing Practice (GMP) standards. This production site was recently inspected by the Dutch Health Care Inspectorate and is licensed to manufacture tracers for human use according to the latest EU guidelines. This site has also been audited by the largest EU pharma companies.

The procedures for radiolabeling of cetuximab with  $^{89}\text{Zr}$  have been validated with respect to the final quality of the prepared conjugate. In three independent labeling experiments, the percentage of label bound to the antibody as assessed by ITLC, HPLC and SDS-PAGE should always be > 90%, preferably > 95%, while the immunoreactive fraction as assessed by cell binding assay, should always exceed 50%, preferably 70%. This analysis will be performed according to a procedure essentially as described by Lindmo et al (Lindmo 1984). In this clinical investigation the radiochemical purity of each  $^{89}\text{Zr}$ -labeled antibody batch prepared will be assessed by ITLC or HPLC and should be more than 90% to allow administration to a patient.

Sterility of each  $^{89}\text{Zr}$ -labeled cetuximab batch will be assured by performing a media fill immediately after final filter sterilization of each batch. In addition, pyrogen testing will be performed according to European Pharmacope. In general, the expiration time of conjugates is 36 hours.

#### Radiation exposure

For the patient the total dose of Zirconium-89 is 37 MBq. After injection no shielding is required, and the patient can go directly home. There are no limitations to the adult residence of the patients. However the first 2 days the patient is not allowed in the proximity of children and pregnant women, and the first two weeks restricted to spend more than 4 hours a day in the same room with children and pregnant women. Also the first week it is advised to retain distance to children and pregnant women.

### 6.2 Drug accountability cetuximab

Unlabelled cetuximab will be obtained from the hospital pharmacist. Cetuximab is supplied as standard and will be prescribed in the outpatient clinic of the department of Medical Oncology at the VUMc. With regard to the  $^{89}\text{Zr}$ -labelled cetuximab, thirty-six hours may elapse between radiolabeling of the compound and administration to the patient.

## 7 Statistical considerations

### 7.1 Evaluation - type of variable

1. Uptake of  $^{89}\text{Zr}$ -cetuximab in non-hepatic tumor lesions (present/absent)
2. Uptake of  $^{89}\text{Zr}$ -cetuximab in non-hepatic tumor lesions (% of total dose injected) (continuous)
3. Uptake of  $^{89}\text{Zr}$ -cetuximab in liver (% of total dose injected)
4. Response according to RECIST 1.1 (categories)
5. Response according to % change of non-hepatic tumor lesion long axis / lymph node short axis
6. [18F]-FDG  $\text{SUV}_{\text{max}}$
7. Grade skin toxicity
8. Serum magnesium level

### 7.2 Statistical design and analysis

#### 7.2.1 Part one

Primary endpoint: maximum 11 patients + 1 allowing for drop-outs = 12

Statistical design: probability

We will analyze  $^{89}\text{Zr}$ -cetuximab uptake in non-hepatic tumor lesions as binary variable (present/absent). We assume that all patients with response (i.e. complete response and partial response) according to RECIST 1.1 criteria and half the patients with stable disease according to RECIST 1.1 criteria will show uptake. According to previous publications we estimate that  $\geq 10\%$  of patients will show response and 30% have stable disease. Thus assuming that the proportion of patients with uptake is 0.25 or more, the probability of seeing no uptake in a cohort of 11 patients is less than 0.05. This has been calculated using a binomial distribution ( $n=11$ ,  $p=0.25$ ).

Stopping rule: The trial will stop if 11 patients do not show uptake. The trial will proceed to part two when the first patient with uptake is seen.

#### 7.2.2 Part two

Primary endpoint: 35 patients (including all patients of part one) + 3 allowing for drop-outs = 38

Statistical design: Comparison of two independent groups of binary data

We are planning a study of independent cases (= all patients with complete response, partial response and stable disease according to RECIST 1.1 criteria) and controls (= patients with progressive disease according to RECIST 1.1 criteria) with 1.5 control(s) per case. We assume a false positive rate of 0.2 in the true negative's (= patients with progressive disease according to RECIST 1.1 criteria) because other downstream targets of the EGFR/RAS pathway may be mutated, thus interfering with response to cetuximab treatment. Measurement of cetuximab uptake using  $^{89}\text{Zr}$ -cetuximab will only be clinically relevant if we identify  $\geq 70\%$  of patients correctly as failures to treatment. Type I error probability has been set at 0.1, the power at 0.9. We will use a continuity-corrected chi-squared statistic or Fisher's exact test to evaluate this null hypothesis.

### Secondary endpoints:

1. The explained variation of % change in tumor axis (short axis for lymph nodes, long axis for non-hepatic metastatic lesions) explained by % (of total injected)  $^{89}\text{Zr}$ -cetuximab uptake in the non-hepatic tumor lesions will be analyzed. Depending on the data we will estimate this relationship fitting either a linear or non-linear regression curve.
2. The potential association between % of total injected  $^{89}\text{Zr}$ -cetuximab uptake in the liver and % uptake in the non-hepatic tumor lesions will be analyzed by linear regression models.
3. The potential association of the change in [18F]-FDG  $\text{SUV}_{\text{max}}$  and response according to RECIST 1.1 will be analyzed with a comparison of the mean using ANOVA or Kruskal-Wallis depending on the distribution.
4. The potential association between grade of skin toxicity and % (of total injected)  $^{89}\text{Zr}$ -cetuximab uptake in the non-hepatic tumor lesions will be analyzed with a comparison of the mean using ANOVA or Kruskal-Wallis depending on the distribution.

